### Main aims

2.1

The main aims of this study are as follows:

To evaluate the effect of daily phytate intake on cognitive ability and compare it with the placebo group.To determine the effect of daily phytate intake on morphological changes and iron storage associated with cognitive impairment in diabetes by magnetic resonance imaging (MRI).

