### The main variables (according to the main objectives) will be the following:

5.1

Progression of cognitive impairment as a dichotomous variable defined as a score decrease >1 SD in MoCA or in any of the cognitive domains studied [visual scanning and processing speed (DSST, TMT-A), divided attention and executive function (TMT-B and verbal fluency), learning, retention memory and verbal recall (RAVLT), praxia, visual memory (ROCF) and language (BNT)] at week 0 and week 56.Differences in the quantification of the iron deposit assessed by nuclear magnetic resonance (NMR) (T2W (R2* and R’2; QSM) (General Electrics, Signa Explorer 1.5T) at week 0 and week 56. We quantify iron content in specific brain areas using magnetic resonance imaging (MRI) techniques such as quantitative susceptibility mapping (QSM) or R2* relaxometry (53). QSM describes the magnetizability of a material to an applied magnetic field and is a substance-specific value (54). Iron causes MRI images to darken at a rate proportional to the iron load, with the half-life of this darkening defined as T2* (55). The rate of darkening, designated as R2*, is the reciprocal of T2* and is proportional to the iron content of the tissues (55). MRI scanning estimates tissue iron concentration both by gradient echo imaging, which provides T2*, and spin echo imaging, which provides T2, the reciprocal of R2 (55). Novel NMR techniques allowed an improvement of tissue metal mapping methods and also the understanding of the ferroptosis mechanisms (53, 55).

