### The secondary variables (depending on the secondary objectives) will be the following:

5.2

Quantitative differences detected by the different cognitive tests (W0 and W56).Morphological differences in the MRI without contrast (W0 and W56): degree of atrophy of the medial temporal lobe (Scheltens score) (56), periventricular intensity and hyperintense lesions in deep white matter (Fazekas scale) (57), and number of lacunar infarcts detected.Differences in retinal neurodegeneration parameters and evolution of diabetic retinopathy (W0 and W56).Retinal function: best-corrected visual acuity (BCVA) and macular perimetry.Structural evaluation of the retina:Seven-field retinography and staging of diabetic retinopathy according to the Early Treatment Diabetic Retinopathy Study (58). Image of the disk-centered fundus, used to study the caliber and morphology of the vessels.Wide-field images with and without fluorescein to examine the peripheral retina and the degree of hypoperfusion (59) ^(^
60
^),^.Optical coherence tomography (OCT-SD) to assess neurodegeneration and macular edema parameters such as retinal nerve fiber layer (RNFL) thickness, ganglion cell layer (GCL) thickness, and choroidal thickness will be collected (61).OCT-angiography: to evaluate in detail the capillary plexuses of the macula, both the vessel density (VD), perfusion density (PD) in both superficial capillary plexus, and the foveal avascular zone (FAZ) will be collected (60).Effect on AD biomarkers (W0 and W56):Inflammation mediators: TNF-a, IL-1b, and IL-6 (Multiplex)Neuronal injury markers: neurofilament (NF) (SimoaTM)AD biomarkers: t-tau, p-tau181, Ab42 and Ab40 (ELISA)AGEs and RAGEs (ELISA)Differences in sleep quality reported by Pittsburg Sleep Quality Index.Differences body composition assessed with vectorial bio-impedance analysis and Nutritional Ultrasound to measure the diameter of the rectus femoris of the quadriceps and preperitoneal visceral adipose tissue.Effect on hand grip strength dynamometry in the dominant and contralateral hand.

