### Statistical analysis

5.4

For the analysis of primary and secondary objectives, differences within groups will be assessed using ANOVA for repeated measures, and difference between groups will be assessed using ANCOVA for repeated measures. Qualitative variables will be analyzed using the chi-square test or the McNemar’s test. The analysis will be adjusted for confounding variables. With regard gender dimension, women have a higher risk of dementia; therefore, an additional analysis will be carried out, stratifying results by sex. A value of p<0.05 will be considered an indicator of a significant difference. The analysis will be performed using SPSS software (IBM Corp., version 24.0).

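### Two main variables share an unadjusted p<0.05 with no hierarchy, and the brain-iron one has no deciding measure, so a main-endpoint claim is not held to a 5% error rate

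*Protocol article*

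**What the plan says.** Section 5.1 of the protocol article opens with "The main variables (according to the main objectives) will be the following" and lists two. The first is "Progression of cognitive impairment as a dichotomous variable defined as a score decrease >1 SD in MoCA or in any of the cognitive domains studied", a single yes/no outcome per patient. The second is "Differences in the quantification of the iron deposit assessed by nuclear magnetic resonance (NMR", followed by R2*, R'2 and QSM in brackets. The same item then says "We quantify iron content in specific brain areas using magnetic resonance imaging (MRI) techniques such as quantitative susceptibility mapping (QSM) or R2* relaxometry", which leaves out R'2, joins the other two by an open choice and names no region.

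Section 5.4 treats primary and secondary objectives together: "For the analysis of primary and secondary objectives, differences within groups will be assessed using ANOVA for repeated measures", with repeated-measures ANCOVA between groups and chi-square or McNemar tests for qualitative variables. The only decision rule is "A value of p<0.05 will be considered an indicator of a significant difference".

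The sample size in section 3.4 uses a two-sided alpha of 0.05 and 80% power, and rests on cognitive progression alone.

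The aims and the variables are sorted differently. Main aim 2 in section 2.1 reads "To determine the effect of daily phytate intake on morphological changes and iron storage associated with cognitive impairment". Section 5.2 puts "Morphological differences in the MRI without contrast (W0 and W56") among the secondary variables, while the secondary aims in section 2.2 do not mention brain morphology.

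**The concern.** With two main variables, each judged at 0.05, and nothing that ranks or combines them, the plan gives two chances to report a significant main result. The second chance is itself open: three metrics are listed, the regions are not named, and no one combination is marked as the main iron result. A null cognitive result could stand beside one significant iron map in one region, and the text would not prevent that map from being reported as a main finding.

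At stake is the error rate of the statement that the trial met a main endpoint. The article presents this as the first randomised trial of phytate in cognitive decline, so there would be no earlier trial to set such a result against.

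**Working it through.** **Plan's own figure.** The article states no family-wise error rate. The only error rate given is 0.05 per test (section 5.4), so there is no figure to reproduce.

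**Inputs from the document.** Two main variables; one binary cognitive outcome, hence one between-arm test; three listed iron metrics (section 5.1); 0.05 for each test.

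**Assumptions.** The number of regions, the correlation between tests, and that success on either main variable counts as a main finding. Within-arm tests and MRI morphology are not counted.

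**Step 1: independent tests.** The chance of at least one false positive in k tests is 1 − 0.95^k.
- k = 2 (cognition and one iron measure): 1 − 0.9025 = 9.75%. The bound under any dependence is 2 × 0.05 = 10%.
- k = 4 (cognition and three metrics in one region): 1 − 0.8145 = 18.5%.

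**Step 2: correlated tests.** These come from simulating correlated two-sided z-tests. For two tests, r is the correlation between cognition and iron. In the other rows, r is the correlation among the iron tests and cognition is independent of them.

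| Tests | Independent | r = 0.8 | r = 0.9 |
|---|---|---|---|
| Cognition + 1 iron measure | 9.75% | 7.8% | 7.1% |
| Cognition + 3 metrics, 1 region | 18.5% | 14.4% | 12.9% |
| Cognition + 3 metrics, 2 regions (assumed) | 30.2% | 18.2% | 15.2% |
| Cognition + 3 metrics, 4 regions (assumed) | 48.7% | 22.6% | 17.8% |

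The first row uses only the document's count of main variables, and the second adds its count of metrics. The last two only show the direction, because the document gives no number of regions.

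**Step 3: is ordering enough by itself?** Suppose cognition is tested first and is truly improved. If iron is then read on three independent metrics at 0.05 each, the iron step alone carries 1 − 0.95^3 = 14.3%. The testing order must therefore be combined with a single named iron measure.

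**Step 4: power cost of splitting alpha.** Section 8 plans 60 per arm; with 15% losses, 60 × 0.85 = 51 are evaluable. Section 3.4 gives a 30% difference without a control rate and without saying whether it is absolute or relative. Reading it as 30 points, with assumed control rates:

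n per arm = [z(1−α/2)·√(2p̄(1−p̄)) + z(0.80)·√(p1(1−p1) + p2(1−p2))]² / (p1 − p2)²

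- 50% vs 20%, α = 0.05: (1.960 × 0.6745 + 0.8416 × 0.6403)² / 0.09 = 38.5, so 39.
- 50% vs 20%, α = 0.025: (2.241 × 0.6745 + 0.8416 × 0.6403)² / 0.09 = 46.7, so 47; 47/0.85 gives 56 recruited.
- 60% vs 30%, α = 0.025: (2.241 × 0.7036 + 0.8416 × 0.6708)² / 0.09 = 50.96, so 51; 51/0.85 = 60 recruited.

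Power at 51 per arm falls from 90% to 84% in the 50% vs 20% case, and from 87% to 80% in the 60% vs 30% case. Over assumed control rates of 30% to 65%, power at 0.025 runs from 98.6% down to 79.6%.

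**The case against.** The strongest reply is that a condensed article may leave the regions, the deciding map and the multiplicity procedure to a full protocol, imaging manual or analysis plan. That stands in part: silence on regions alone would not be a finding. But section 5.4 states a threshold and applies it to primary and secondary objectives alike, and section 5.1 gives two differing lists of iron metrics. A later document would have to override this text, not merely add to it.

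A second reply is that no passage says either variable is enough for success. That is correct, and the inflation is conditional on it; if both had to succeed there would be none. The abstract and introduction put cognition first and iron after it, and the sample size rests on cognition. This suggests an order but is not a testing rule.

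A reader might infer three stronger points that the document does not support:
- That the cognitive efficacy claim itself loses its 5% protection. It does not. Cognitive progression is one binary variable with one between-arm test, and its error rate is the same however many iron maps are read. A false iron result is a false iron claim.
- That the error rate approaches one half. The 48.7% figure needs four regions, which the document does not give, and 13 independent tests, although the metrics measure the same quantity in the same brains. At correlations of 0.8 to 0.9 the same case gives about 18% to 23%.
- That MRI morphology is a third main endpoint. Section 5.2 classifies it as secondary. The mismatch with section 2.1 is real, but it is a matter of wording.

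Basing the sample size on only one of two main variables is not in itself an error.

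**Conclusion.** The point holds as a matter of moderate importance. As written, two main variables are each tested at an unadjusted 0.05, and the iron variable has no deciding metric or region. If either can support a main claim, the chance of at least one false main finding is about 7% to 10% with a single iron measure. It is about 13% to 19% with the three listed metrics in one region, taking cognition as independent of iron. More regions raise it further by an amount the document does not allow one to fix. Every case computed exceeds 5%, so the conclusion does not depend on the assumed number of regions or on independence. It does depend on the either-variable reading, which the text permits but does not state.

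**What to change.** Before unblinding:

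1. State in section 5.4 that cognitive progression, the variable behind the sample size, is tested first at two-sided 0.05, and that iron is tested at 0.05 only if cognition is significant. Holm's procedure or 0.025 for each variable would also hold the family-wise rate to 5%.
2. Name in section 5.1 one iron metric and one set of regions as the deciding measure. Which one is the sponsor's choice; the document does not favour QSM over R2* or the reverse. Report the remaining metrics and regions as exploratory.
3. Bring section 2.1 into line with section 5.2 by moving MRI morphology to the secondary aims in section 2.2.

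These are wording changes. The fixed sequence needs no extra patients, but iron alone could then no longer give a confirmatory main result. The equal split keeps that possibility and costs about 6 to 7 percentage points of power for cognition in the two assumed scenarios, leaving about 80% to 84% with 51 evaluable per arm. Those powers hold only if the 30% difference is absolute. If it is relative, for example 50% vs 35%, about 170 evaluable per arm would be needed even at 0.05, so power would be short with or without the split.

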### Ethical considerations

5.5

The clinical researchers involved in the trial have a valid certificate of Good Clinical Practice. The study will adhere to law 14/2007 on biomedical research, the principles of the Declaration of Helsinki, and the Council of Europe Convention on Human rights and Biomedicine. Our protocol has been approved by the Ethics and Clinical Research Committee of the Balearic Islands (CEI-IB) with number “IB4719/21”. The study will be carried out according to the standards of Good Clinical Practice and Guidelines of the International Conference on Harmonization (ICH).

## Safety

6

The treatment that is used, Lit-Control^®^ pH Balance, has been developed with ingredients that have been internationally recognized as safe. No incidents have been reported by its consumers since the beginning of its commercialization on said date. However, in case that a possible serious adverse event was to be detected and recorded, the treatment would be suspended and the investigator would proceed as follows:

- The sponsor would be immediately informed of all adverse events. Immediate notification must be followed by timely detailed written reports. The immediate and follow-up report must identify subjects by a unique code assigned to the trial subject and not by the subject’s name, personal identification numbers, or subject’s address. The investigator must also comply with the legal regulations regarding the notification of serious and unexpected adverse events to the relevant authorities and to the CEI-IB.- When the researcher notifies a death, he must provide the promoter and the CEI-IB with all the complementary information that they request (e.g., the autopsy report and the most recent medical reports). An adverse event (AE) will be considered any adverse health incident that occurs in a patient who has received a treatment, even where there is not necessarily a causal relationship with said treatment. An adverse event (AE) can therefore be any unfavorable and unintended sign (including an abnormal laboratory finding), symptom, or disease temporarily associated with the use of treatment, whether or not related to it.

According to current regulations, “serious adverse events” will be considered as “any adverse reaction that causes death, may be life-threatening, requires hospitalization of the patient or prolongation of existing hospitalization, causes significant or persistent disability or invalidity, or constitutes a congenital anomaly or birth defect. Those suspected adverse reactions that are considered important from a medical point of view, even if they do not meet the above criteria, such as those that put the patient at risk, or require intervention to prevent any of the above outcomes, will also be treated as serious, as will all suspicions of transmission of an infectious agent through a medication (RD 1090/2015, art. 22.1.d “Serious adverse reaction”)”.

## Validity and reliability

7

The current study will provide important information on the effect of oral phytate supplementation on cognitive impairment progression, cerebral iron deposition, and diabetic retinopathy on patients living with T2DM. The PHYND study will include a control sample of participants that will receive placebo. The free-living conditions and the study design will allow us to obtain robust results. Internal validity will be warranted by a randomization process based on allocation sequence generation, blinded to the PI and staff involved in the intervention. Moreover, the data analyst and the PI will be blinded to patient allocation to reduce biases in the evaluation of the intervention. Lastly, the interventions are based on the latest scientific evidence.

## Discussion

8

The present study will provide information on the efficacy of an oral phytate supplementation intervention (≈1g/day) to reduce cognitive impairment progression, cerebral iron deposition, and diabetic retinopathy on patients living with T2DM. There is no specific treatment available to reduce cognitive impairment progression on patients with T2DM. Diets known to be high in phytate are associated with lower cognitive decline (33). So far, there is no randomized clinical trial assessing the effect of phytate intake in cognitive decline and neurodegenerative disease. Our work will be the first one in assessing the effects of oral phytate supplementation in amounts corresponding to a healthy and balanced diet rich in nuts and legumes (≈1g/day) on cognitive impairment progression in outpatients conditions.

The PHYND study presents some limitations. First, it focuses on patients with T2DM and MCI, potentially restricting the generalizability of results to broader populations. Second, ensuring participant compliance with the daily phytate supplementation regimen is crucial, yet despite monitoring mechanisms like pill counts and urinary phytate level assessments, inconsistent adherence may impact result interpretation. Third, despite rigorous blinding procedures and the use of validated outcome measures to minimize placebo effects, improvements related to the placebo effect within the placebo group are still possible, which could influence the interpretation of study outcomes. The most important limitation will be patient adherence to the treatment and the study, given its length, i.e., 56 weeks of intervention. However, this issue will be mitigated by frequent follow-up, frequently telephonic reminders of the appointments, and motivational interview. Another issue is the small sample size. We anticipate a 15% drop off based on other dietary intervention studies on MCI considering an alpha risk of 0.05 and a statistical power of 0.8(49); a minimum sample of 45 T2DM patients is required. Keeping this in mind, we will recruit 60 patients per arm. Thus, reducing the probability of small sample is a limitation of our work. In addition, as the study is single center (the sample will be taken at the Endocrinology and Nutrition service of the Son Llàtzer Hospital), we are aware that it could not be possible to generalize the results obtained.

However the strengths of our work are a multidisciplinary approach, where the effect of phytate supplementation on the brain and the retina will be objectively examined using validated ophthalmic tests, magnetic resonance imaging iron measurement, evaluation of cognitive impairment through validated psychological tests, extensive laboratory tests (using the accepted laboratory parameters, inflammatory mediators, markers of neuronal injury, AD biomarkers, and advanced glycation products), and measurement of body composition and strength using nutritional ultrasound and bio-impedance vector analysis and dynamometry. In addition, as the cognitive status of participants can be influenced by depression, educational level and quality, and quantity of sleep, this information will be collected with validated tests. Phytate levels will be monitored by measuring adherence to diet supplementation and serial measurement of urinary phytate levels.

Finally, the results of our study could contribute to better nutritional strategies for the management of cognitive impairment and diabetic-related complications. Given the increasing prevalence of T2DM and cognitive impairment, determining interventions that could prevent or reduce diabetes-related complications and reduce the progression of cognitive impairment could have a great impact on the lives of our population.

## Ethics statement

The studies involving humans were approved by Ethics and Clinical Research Committee of the Balearic Islands (CEI-IB) with number “IB4719/21”. The studies were conducted in accordance with the local legislation and institutional requirements. Written informed consent for participation was not required from the participants or the participants’ legal guardians/next of kin in accordance with the national legislation and institutional requirements.
